## Abstract

**Background:**

Insomnia is a global disease with a high incidence and acupuncture therapy is a well appropriate method to treat insomnia. Shenmen (HT 7) and Sanyinjiao (SP 6) are the acupoints most commonly used to treat insomnia. Although they can obviously relieve the clinical symptoms of insomnia, it is unclear whether they must be used together, whether the combination of two acupoints may have a synergistic or antagonistic effect, and whether there is a primary or secondary relationship between the two points in the treatment of insomnia. Further studies are needed. Therefore, in this study, we are exploring the acupoint combination effect and biological mechanism of HT 7 and SP 6 in treating insomnia.

**Methods/design:**

This will be a parallel group randomized controlled trial. The study will recruit 120 patients with insomnia randomly assigned to a control group, an electroacupuncture on HT 7 group, an electroacupuncture on SP 6 group, and an electroacupuncture on HT 7 and SP 6 group. The allocation ratio is 1:1:1:1, with 30 subjects in each group. Meanwhile, ten healthy subjects who meet the study criteria will be recruited as the healthy control group. Patients in the intervention groups will be given ten rounds of electroacupuncture stimulation on the corresponding acupoints for 2 weeks, five times per week, with 2 days of rest between the two treatment courses. Patients in the control group will also receive the same two courses of ten rounds of compensatory acupuncture therapy after a 2-week waiting period for treatment. The major outcome measures of this study include the Sleep Dysfunction Rating Scale, the Insomnia Severity Index, Epworth Sleepiness Scale, the Zung Self-Rating Anxiety Scale, and the Zung Self-Rating Depression Scale, combined with the Measure Your Medical Outcome Profile, to evaluate insomnia and the emotional state of patients with insomnia. The secondary outcome measures include sleep composition monitored by polysomnography and measurements of acetylcholine, serotonin, dopamine, norepinephrine, melatonin, gamma-aminobutyric acid, and metabolic biomarkers in serum.

**Discussion:**

In this study, we are exploring the acupoint combination effect and biological mechanism of HT 7 and SP 6 in treating insomnia, which may provide evidence for the clinical application of acupuncture and acupoint selection in the treatment of insomnia.

**Trial registration:**

Chinese Clinical Trial Registry, Chi-CTR-1800017483. Registered on 1 August 2018.

## Background

Acupoint combination is a method to improve clinical curative effects by combining two or more acupoints to achieve specific therapeutic effects [1]. It is a very important factor affecting clinical curative effect. Maximizing the efficacy of acupoint combination is the key to improving the curative effect of acupuncture and moxibustion [2].

Insomnia is a global disease with a high incidence. The incidence is above 35% in recent years [3, 4]. Insomnia is a serious deterioration of sleep quality, usually accompanied with serious residual effects during the daytime, including dizziness, headache, malaise, fatigue, anxiety, and other symptoms, which may reduce quality of life and activity efficiency, affect physical and mental health, and even cause many kinds of diseases [5].

Acupuncture has a long history and advantages in treating insomnia. According to statistics, 156 prescriptions and 90 acupuncture points for insomnia treatment are recorded in ancient books [6]. The acupoints selections for insomnia also reflect the idea of acupoint combination. Many clinical reports show that acupuncture therapy has definite curative effects on insomnia and certain advantages over conventional drugs [7, 8]. Studies have shown that Shenmen (HT 7) and Sanyinjiao (SP 6) are the two most frequently used acupoints for insomnia treatment [9–13]. What’s more, the two acupoints were the most common combination, the support degree of their simultaneous appearance was 59.40% among the 266 prescriptions reported from 1994 to 2014 [9]. From traditional Chinese medicine (TCM) theory, HT 7 is the original point of the heart meridian, with the function of nourishing heart zang and tranquilizing the mind, which are good for sleep. SP 6 belongs to the spleen channel, being the intersection of liver, kidney, and spleen channels, with the function of coordinating and reinforcing qi and blood, which helps to nourish heart zang and soothe the nerves to improve sleep. The combination of HT 7 and SP 6 has the effect of harmonizing yin and yang, calming heart and soothing the nerves, to bring peaceful sleep. It was found that electroacupuncture stimulation on HT 7 and SP 6 has good effects on the sympathetic adrenal medullary system and improves anxiety in a rat insomnia model [14, 15]

Previous studies mainly count the frequency of the selections and collocation of them, which is not enough to reflect the deeper law of acupoint combination in treating insomnia. Because the law, effect, and mechanism of it are not thoroughly studied [16], and because of the lack of experimental evidence [17], there is a certain gap between acupoint combination research and clinical application of acupuncture therapy.

Although HT 7 and SP 6 can relieve clinical symptoms and adjust neuroendocrine function of patients with insomnia, further studies are needed, such as whether they must be used together, whether the combination of two acupoints may have a synergistic or antagonistic effect, and the primary and secondary relationships between the two points in the treatment of insomnia. This study will analyze the curative effect of the combination of HT 7 and SP 6 in treating insomnia and will reveal the biological mechanism at the metabolic level. The results can provide evidence for selection of acupoints to treat insomnia and accumulate experience for exploring the effect and mechanism of acupoint combination.

## Methods/design

### Study design

This will be a parallel group randomized controlled trial. The study will recruit 120 patients with insomnia from the Affiliated Hospital of Chengdu University of TCM and the Third Affiliated Hospital of Chengdu University of TCM. Meanwhile, ten healthy subjects who meet the study criteria will be recruited as the healthy control group. The patients enrolled will be randomly assigned to a control group, an electroacupuncture on HT 7 group (EA-SM group), an electroacupuncture on SP 6 group (EA-SY group), and an electroacupuncture on HT 7 and SP 6 group (EA-SS group). The allocation ratio is 1:1:1:1, with 30 subjects in each group. All patients will be asked to sign the consent form before the trial. Patients in the intervention groups will be given ten rounds of electroacupuncture stimulation on corresponding acupoints for 2 weeks, five times per week, with 2 days of rest between the two treatment courses. Patients in the control group will also receive the same two courses, ten rounds of compensatory acupuncture therapy after the 2-week waiting period for treatment. The healthy control group will not be given any intervention. The overall schematic and study design are presented in Fig. 1, and the schedule of enrollment, intervention, and assessments is shown in Fig. 2, according to the Standard Protocol Items: Recommendations for Interventional Trials (SPIRIT) 2013 statement [18].

**Fig. 1 Fig1:**
[figure not shown]
Overall schematic chart of the study. The template is a Consolidated Standards of Reporting Trials (CONSORT) 2010 flow diagram. *EA-SM Group* electroacupuncture on Shenmen (HT 7), *EA-SY Group* electroacupuncture on Sanyinjiao (SP 6), *EA-SS Group* electroacupuncture on Shenmen (HT 7) and Sanyinjiao (SP 6), *SDRS* Sleep Dysfunction Rating Scale, *ISI* Insomnia Severity Index, *ESS* Epworth Sleepiness Scale, *SAS* Zung Self-Rating Anxiety Scale, *SDS* Zung Self-Rating Depression Scale

**Fig. 2 Fig2:**
[figure not shown]
Study schedule of enrollment, interventions, and assessments. The template is derived from the Standard Protocol Items: Recommendations for Interventional Trials (SPIRIT) 2013 statement. The patients in the control group will finish the assessments and then receive compensatory acupuncture therapy at week 3 after the 2-week waiting period (week 1, week 2). *EA-SM Group* electroacupuncture on Shenmen (HT 7), *EA-SY Group* electroacupuncture on Sanyinjiao (SP 6), *EA-SS Group* electroacupuncture on Shenmen (HT 7) and Sanyinjiao (SP 6), *SDRS* Sleep Dysfunction Rating Scale, *ISI* Insomnia Severity Index, *ESS* Epworth Sleepiness Scale, *SAS* Zung Self-Rating Anxiety Scale, *SDS* Zung Self-Rating Depression Scale, *PSG* polysomnography

## Participants

### Criteria for patients with insomnia

#### Inclusion criteria

We will include patients who (1) meet the diagnostic criteria for insomnia (referring to the guidelines for the diagnosis and treatment of adult insomnia in China drawn up by the Sleep Disorders Group of Chinese Neurology Society [19]), (2) are aged 20–60 years (either sex), and (3) have received a full explanation about the research and have signed the informed consent form.

#### Exclusion criteria

Participants with any of the following conditions will be excluded from this trial: (1) secondary insomnia caused by physical disease or mental disorder; (2) those who refuse acupuncture therapy; (3) insomnia during pregnancy or lactation; (4) those who have received other sleep-related treatment within 2 weeks before the study; and (5) patients with cardiovascular, pulmonary, liver, kidney, hematopoietic, or other serious primary diseases and mental diseases.

### Criteria for healthy control subjects

#### Inclusion criteria

Inclusion criteria for healthy control subjects include: (1) without any physical or mental illness; (2) routine blood examination for liver function, kidney function, electrocardiogram, blood glucose, and lipids are normal; (3) aged from 20 to 60 years old (either sex); (4) have not participated in other clinical studies recently; (5) have signed the informed consent form and volunteered to participate in this study.

#### Exclusion criteria

Subjects will be excluded if they have any of the following conditions: (1) women during menstruation, pregnancy, or lactation and (2) alcoholism or heavy smoking.

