### Sample size

This study sample size is calculated on the basis of a ratio of 1:1:1:1 between the intervention groups and the control group. Though there are four study groups, the study can be regarded as a comparison between each intervention group and the control group. This study refers to the method of sample size estimation in this paper [20]. In those studies, the sample sizes are based on studies that investigated the effect of acupuncture-related treatment on insomnia using the Sleep Dysfunction Rating Scale (SDRS) as a major outcome [21, 22], and the number of participants required for each group is 30 or 31. In addition, in the study [21], the mean change in SDRS between the intervention and control groups was 2.69, and the standard deviation was estimated from the means and the standard deviations of intervention (− 14.80 ± 3.52) and control groups (− 12.11 ± 2.38). On the basis of a two-tailed alpha error of 5% and with a statistical power of 90%, the calculated sample size is based on the equation:
$$ N=\frac{2\times {\left(\frac{Z\alpha}{2}+ Z\beta \right)}^2\times {\sigma}^2}{\delta^2} $$$$ N=\frac{2\times {\left(1.96+1.28\right)}^2\times {3.00}^2}{2.69^2}=26.11 $$

Therefore, this study’s sample size is 120, assuming a 15% dropout rate, and all 120 participants will be randomly assigned, with 30 subjects in each group.

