## Data analysis

Statistical analysis includes the actual number of subjects, cases of shedding and exclusion, demographic and other baseline characteristics, compliance analysis, safety assessment, insomnia and emotional state scores, SL, TST, and quantity analysis of serum neurotransmitters and hormones. IBM SPSS Statistics for Windows version 19.0 software (IBM Corp., Armonk, NY, USA) will be used for statistical analysis. We will adopt univariate analysis of variance to analyze the age, height, weight, scale score, SL, TST, neurotransmitter and hormone content, and so forth, and we will use the chi-square test to analyze gender comparison and the rank-sum test to analyze the course of disease. *P* < 0.05 will be considered as the standard of statistical significance. Serum will be analyzed by liquid chromatography–mass spectrometry, and the serum metabolic biomarkers of insomnia will be screened using MetaX metabolomic data analysis software (BGI Genomics Co. Ltd., Shenzhen, China).

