## Discussion

This study is a parallel group randomized controlled trial exploring the effects and mechanisms of acupoint combination of HT 7 and SP 6 for treating insomnia. Multiple scales are used to comprehensively evaluate patients’ sleep quality at night and their energy and emotional state during daytime, including SDRS, ISI, ESS, SAS, and SDS. PSG is a common method of neural electrophysiological monitoring in sleep research that is often used for objective analysis of sleep. It not only can analyze the sleep structure and sleep phase of patients and reflect the degree of insomnia but also analyze the corresponding changes in heart, breathing, and muscle activity while sleeping. This study observes the effects of a single use of HT 7 or SP 6 and the joint use of the two acupoints for treating insomnia from multiple perspectives, according to subjective self-perception and objective sleep structure of patients with insomnia by using multiple scales and PSG.

Multiple nerve centers and neurotransmitters take part in the regulation of sleep. Studies have shown that the human body clock system (e.g., suprachiasmatic nucleus) periodically stimulates the sleep-inducing area and the wake-inducing area and inhibits or facilitates the cerebral cortex through the ascending inhibitory system or activation system, resulting in sleep or wakefulness [25]. Ach, 5-HT, DA, and NE may play a crucial part in sleep regulation in the sleep inhibitory or activation systems [26]. In addition, MT and GABA also play an important role. So, this study will quantify the Ach, 5-HT, DA, NE, MT, and GABA in serum of subjects in the healthy control group, the control group, and the three intervention groups using enzyme-linked immunosorbent assays to explore the neurotransmitter regulatory mechanism of the effect that improves sleep by acupoint combination.

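### Healthy controls face entry limits that patients do not, so the insomnia biomarker contrast can partly reflect selection; keep this group out of treatment tests and adjust the contrast

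*Protocol article*

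**What the plan says.** **Who the healthy controls are.** Under the criteria for healthy control subjects, the ten volunteers must be free of physical and mental illness, aged 20 to 60, and pass the requirement that "routine blood examination for liver function, kidney function, electrocardiogram, blood glucose, and lipids are normal". The exclusion list adds "women during menstruation, pregnancy, or lactation and (2) alcoholism or heavy smoking".

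**Who the patients are.** The age range is the same and either sex is eligible. The exclusions include "insomnia during pregnancy or lactation", insomnia secondary to physical or mental disorder, serious organ disease and mental disease. There is no criterion on smoking, menstruation or normal laboratory values, and none that names alcohol.

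**How the healthy group is used.** Data analysis states that "the serum metabolic biomarkers of insomnia will be screened using MetaX metabolomic data analysis software". The limitations paragraph of the Discussion confirms that healthy controls and patients are compared by untargeted metabolomics. The Discussion also says that transmitters and melatonin will be measured "in serum of subjects in the healthy control group, the control group, and the three intervention groups". For these the only stated method is univariate analysis of variance, without naming the groups that enter it. No matching or covariate is mentioned.

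**The concern.** Two uses of the healthy group need to be kept apart.

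The first is the search for markers that separate insomnia from health. Here the controls are selected on glucose and lipids, which belong to the chemistry that a serum assay reads, and on smoking, alcohol and menstruation, which may affect it. A patient who smokes heavily, or whose lipids are abnormal without serious disease, is eligible; an otherwise healthy volunteer with the same feature is not. A marker could therefore differ between the groups because of the entry rules and be reported as a feature of insomnia.

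The second is the effect of acupuncture on serum markers. That question belongs to the four randomised arms. Serum is measured in five groups and the ANOVA is not restricted to four of them, so the text leaves room for a test in which a non-randomised group could drive the result.

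**Working it through.** **1. The plan's own figure.** The Sample size section takes a difference of 2.69 and an SD of 3.00 on the SDRS: "the mean change in SDRS between the intervention and control groups was 2.69". Then 2 × (1.96 + 1.28)² × 3.00² / 2.69² = 26.11 per group, as stated. Allowing for 15% dropout gives 26.11 × 1.15 = 30.03 or 26.11 / 0.85 = 30.7, against 30 planned. This covers the randomised groups only. No size calculation is given for the ten healthy controls.

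**2. Criteria side by side.**

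| Item | Healthy controls | Patients |
|---|---|---|
| Pregnancy, lactation | excluded | excluded |
| Age 20–60, either sex | yes | yes |
| Menstruation | excluded | no limit |
| Heavy smoking | excluded | no limit |
| Alcoholism | excluded | not named; mental-disease exclusion may cover part |
| Glucose, lipids, liver, kidney, ECG | must be normal | only serious disease excluded |

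**3. Precision of 10 versus 120.** The standard error in SD units is √(1/10 + 1/120) = 0.329, so the 95% half-width is 1.96 × 0.329 = 0.65 SD. If ages were uniform over 20–60 (assumed), the SD would be 40/√12 = 11.5 years and the chance gap in mean age would have a 95% range of ±1.96 × 11.5 × 0.329 = ±7.4 years. This gap would arise even with identical criteria. It is a reason to adjust for age, not evidence of selection bias.

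**4. Bias from an exposure excluded in controls only.** Let a share *p* of patients and no control carry an exposure that shifts a marker by *e* SD. The bias is *p* × *e*. The documents give neither quantity, so both are assumed: *p* from 0.10 to 0.40, *e* from 0.5 to 1.0. The bias then runs from 0.10 × 0.5 = 0.05 SD to 0.40 × 1.0 = 0.40 SD. For a two-sided 5% *t* test the noncentrality is bias / √(1/10 + 1/n).

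| Comparison | Rejection at bias 0.05 SD | at 0.20 SD | at 0.40 SD |
|---|---|---|---|
| 10 vs 120 | 5.3% | 9.3% | 22.6% |
| 10 vs 30 | 5.2% | 8.3% | 18.7% |

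The insomnia effect is zero throughout, so the excess over 5% comes from selection alone.

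**5. A five-group F test, if one were run.** Take group sizes 10, 30, 30, 30, 30, equal means in the four patient arms, and a healthy group shifted by *d* SD (assumed). The degrees of freedom are 4 and 125, and the noncentrality is (10 × 120 / 130) × *d*² = 9.23 *d*².

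| *d* | Noncentrality | Probability of rejection |
|---|---|---|
| 0.25 | 0.58 | 7.9% |
| 0.5 | 2.31 | 18.7% |
| 0.8 | 5.91 | 44.7% |
| 1.0 | 9.23 | 65.7% |

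There is no treatment effect in any row.

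**The case against.** **A five-group test is not specified.** A reader might infer from the five-group measurement and the single ANOVA that all five groups share one F test. The documents do not say so. Data analysis names no group set, four groups are randomised, and the Sample size section describes each intervention group against the control group. That last statement concerns the SDRS calculation and does not settle the serum analysis, but it does point away from an omnibus test. The F figures therefore apply only if such a test were run. Even then, rejection caused by a real difference between health and insomnia is not a false positive; it misleads only if read as an acupuncture effect.

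**Confounding is possible, not certain.** A reader might also conclude that the biomarkers will be confounded. Without exposure prevalence or marker effects this cannot be claimed, and at the low end of the assumed range the inflation is negligible. Alcoholism may already be partly excluded among patients.

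**Silence on adjustment is not a statement of no adjustment.** Covariates may be set out in a fuller protocol or analysis plan that is not shown.

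**The work is already presented cautiously.** Serum markers are secondary, and the limitations paragraph calls the metabolomic comparison qualitative and in need of verification. This is fair, but that paragraph does not mention the differing criteria, the ten controls or possible confounding.

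What remains is the asymmetry itself. The article states it outright, and a later analysis plan cannot undo the selection.

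**Conclusion.** The point holds as a risk to the secondary, mechanistic results. The healthy controls are selected on normal laboratory and ECG results, no menstruation and no heavy smoking (and on alcoholism, with the reservation above), and the patients are not. Differences between the groups can therefore partly reflect entry criteria, age or sex. Under the assumed exposures the chance of a spurious marker is between about 5% and 23% per test at a nominal 5%.

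The risk to the treatment question is conditional. If the healthy group entered the same ANOVA as the randomised arms, a significant F could not be attributed to treatment, with rejection of about 8% to 66% for assumed shifts of 0.25 to 1.0 SD. The primary SDRS comparison among the randomised groups is untouched. The change is worth making because it is cheap and concerns how the marker results will be read.

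**What to change.** In Data analysis, separate the two questions:

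- **Treatment effects on serum markers:** test in the four randomised arms only, adjusting for the baseline value where a baseline sample exists. State that the healthy group enters no test of acupuncture effect.
- **Healthy versus insomnia:** use baseline samples only, adjust for age and sex, and report as exploratory. Data analysis already lists both variables, so no new data are needed.

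In the limitations paragraph of the Discussion, state that the eligibility criteria differ and on which items. A sensitivity analysis applying the control exclusions to patients is optional. It is possible only where smoking, alcohol, menstruation and laboratory data were recorded, which the article does not say.

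The cost is slightly more analysis and a more cautious biomarker claim. With 115 participants already recruited and treated according to Trial status, changing eligibility is no longer realistic, but these changes need no new patients or procedures.

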### Sample size

This study sample size is calculated on the basis of a ratio of 1:1:1:1 between the intervention groups and the control group. Though there are four study groups, the study can be regarded as a comparison between each intervention group and the control group. This study refers to the method of sample size estimation in this paper [20]. In those studies, the sample sizes are based on studies that investigated the effect of acupuncture-related treatment on insomnia using the Sleep Dysfunction Rating Scale (SDRS) as a major outcome [21, 22], and the number of participants required for each group is 30 or 31. In addition, in the study [21], the mean change in SDRS between the intervention and control groups was 2.69, and the standard deviation was estimated from the means and the standard deviations of intervention (− 14.80 ± 3.52) and control groups (− 12.11 ± 2.38). On the basis of a two-tailed alpha error of 5% and with a statistical power of 90%, the calculated sample size is based on the equation:
$$ N=\frac{2\times {\left(\frac{Z\alpha}{2}+ Z\beta \right)}^2\times {\sigma}^2}{\delta^2} $$$$ N=\frac{2\times {\left(1.96+1.28\right)}^2\times {3.00}^2}{2.69^2}=26.11 $$

Therefore, this study’s sample size is 120, assuming a 15% dropout rate, and all 120 participants will be randomly assigned, with 30 subjects in each group.

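### Thirty per group does not preserve the plan's own 26.11 evaluable patients at 15% dropout; power there is about 89%, so the sentence needs a minor restatement

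*Protocol article*

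**What the plan says.** All the relevant text is in the Sample size section of the protocol article.

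- **Comparison that is sized.** Although there are four randomised groups, "the study can be regarded as a comparison between each intervention group and the control group". The calculation is therefore for two groups, one pair at a time.
- **Error rates.** "On the basis of a two-tailed alpha error of 5% and with a statistical power of 90" per cent, entered in the formula as 1.96 and 1.28.
- **Effect.** From a cited study, "the mean change in SDRS between the intervention and control groups was 2.69".
- **Standard deviation.** "the standard deviation was estimated from the means and the standard deviations of intervention" and control groups, that is from 3.52 and 2.38; the value entered is 3.00.
- **Result.** 26.11 per group.
- **Size adopted.** "sample size is 120, assuming a 15% dropout rate, and all 120 participants will be randomly assigned, with 30 subjects in each group".

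The article does not show how it goes from 26.11 to 30, and it gives no separate power figure after dropout.

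**The concern.** The section presents 120 as following from the calculation together with the dropout allowance. A reader will take this to mean that if 15% are lost, each group still has the 26.11 evaluable patients that 90% power requires. It does not. An allowance for loss has to satisfy n × (1 − d) ≥ required n, so the required number is divided by 1 − d. Multiplying by 1 + d gives too few.

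What is at stake is the accuracy of a figure that will be cited when the trial is reported. The 90% power, the 15% dropout and the 30 per group cannot all hold exactly under the plan's own formula.

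**Working it through.** **Inputs** (all from the Sample size section): difference δ = 2.69; SD σ = 3.00; z-values 1.96 and 1.28; dropout d = 0.15; 30 randomised per group.

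**1. Reproduce the SD.** √[(3.52² + 2.38²)/2] = √[(12.3904 + 5.6644)/2] = √9.0274 = 3.005. The entered 3.00 is consistent with this.

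**2. Reproduce the plan's figure.** n = 2 × (1.96 + 1.28)² × 3.00² / 2.69² = 26.11. This agrees, and in whole patients it means 27.

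**3. What 30 per group leaves.** 30 × (1 − 0.15) = 25.5, which is 0.61 below 26.11.

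**4. Size that 15% dropout requires.**

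| Starting figure | Divided by 0.85 | Per group | Total |
|---|---|---|---|
| 26.11 | 30.72 | 31 | 124 |
| 27 | 31.76 | 32 | 128 |

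The shortcut gives 26.11 × 1.15 = 30.03, which rounds to the stated 30. That this was the route taken is an inference.

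**5. Dropout that 30 per group can absorb.** Against 26.11: 1 − 26.11/30 = 13.0%. Against 27: 1 − 27/30 = 10.0%.

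**6. Power, by the protocol's own normal approximation.** Power = Φ(δ / [σ√(2/n)] − 1.96). For n = 25.5: 2.69 / [3.00 × √(2/25.5)] = 3.202; 3.202 − 1.96 = 1.242; Φ(1.242) = 0.893.

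| Evaluable per group | Situation | Power per comparison |
|---|---|---|
| 30 | no dropout | 93.5% |
| 27 | 10% dropout | 90.9% |
| 26.11 | about 13% dropout | 90.0% |
| 25.5 | 15% dropout | 89.3% |
| 25 | 25.5 rounded down | 88.7% |

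The shortfall at the stated dropout is 0.7 points, or 1.3 points if 25.5 is rounded down to 25.

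**The case against.** **The effect is negligible.** A shortfall of 0.7 points, from one or two patients per group, is smaller than the uncertainty in δ and σ. This stands, and it is why the point is minor. A t-test calculation gives a lower figure, 88.1% at 25.5, but it gives only 89.9% at the full 27. Part of that gap therefore comes from the normal approximation and not from dropout.

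**Actual dropout looks low.** The Trial status section reports 115 recruited and 115 who completed the intervention. If all are patients with insomnia, equal groups would average 115/4 = 28.75 (power 92.5%). If the count includes all ten healthy controls, which the text does not say, the average is 105/4 = 26.25 (power 90.1%). This largely removes the practical consequence. It does not correct the stated allowance.

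**Dropouts may still be analysed.** The Quality control and guarantee section invokes intention to treat and aims to complete dropouts' evaluations where possible, so 15% dropout need not mean 15% without data. The same section, however, also ties inclusion in the analysis to having received more than half of the treatment. It does not clearly rescue the figure.

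**A slightly smaller SD would suffice.** With the simple average of the two SDs, 2.95, the formula gives 25.25, and 25.25/0.85 = 29.7, so 30. The plan, however, uses 3.00 and prints 26.11.

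**Stronger readings that a reader might infer, and that the document does not support:**

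- *That 90% is overstated because three comparisons share one control.* The section openly states an unadjusted pairwise basis. It claims neither familywise power nor power to succeed in all three comparisons, so lower figures under an adjustment contradict nothing it says. Multiplicity may be handled in an analysis plan that is not shown.
- *That 2.69 is unsuitable because the cited control arm itself changed by −12.11, while this control group waits two weeks.* If a waiting group improved less, the difference from electroacupuncture would be larger than 2.69 and the calculation conservative. The article does not say what the cited control arm received. Nothing in it supports recasting 2.69 as a difference worth detecting between any two groups.

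**Conclusion.** Wrong as written, and minor. The plan's 26.11 reproduces exactly, but 30 per group leaves 25.5 at the stated 15% dropout. Full protection would need 31 per group, or 32 from a rounded 27. Power at that dropout is about 89% for each unadjusted comparison with control, and the 90% claim holds up to about 13% dropout.

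This rests on the protocol's own inputs (δ = 2.69, σ = 3.00, two-sided 5%), its normal formula, equal groups, and dropout meaning loss from the analysed number. It does not show that the trial is underpowered.

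**What to change.** Keep 120 patients, 30 per group, and replace the concluding sentence of the Sample size section with a statement to this effect:

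> With 30 patients per group, the normal-approximation formula above gives 90% power for each unadjusted pairwise comparison of an intervention group with control at up to about 13% dropout (10% if 27 evaluable patients per group are required), and about 89% power at 15% dropout.

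All power figures in the sentence should come from this one formula, so that methods are not mixed. The cost is one sentence: no additional patients and no change to the design or analysis.
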